## Abstract

**Background:**

Job rotation has often been used in situations where the level of exposure cannot be reduced due to the characteristics of the job or through physical measures. However, the effectiveness of the job rotation strategy at preventing musculoskeletal complaints lacks adequate scientific data.

**Methods/Design:**

A cluster randomized controlled trial will be used to investigate the effectiveness of job rotation to prevent musculoskeletal disorders in industrial workers. The randomized cluster was based in characteristics of production sectors. A total cluster will be 4 sectors, and 957 workers will be recruited from a textile industry and randomly allocated into intervention or control groups. Both groups will receive training on ergonomics guidelines. In addition, the intervention group will perform job rotation, switching between tasks with low, moderate, and high risk for musculoskeletal complaints. The primary outcome will be the number of working hours lost due to sick leave by musculoskeletal injuries recorded in employee administrative data bases. Secondary outcomes measured via survey include: body parts with musculoskeletal pain, the intensity of this pain, physical workload, fatigue, general health status, physical activity level, and work productivity. Secondary outcome measures will be assessed at baseline and after 3, 6, 9, and 12 months. The cost-effectiveness analysis will be performed from the societal and company perspective.

**Discussion:**

Prevention of work-related musculoskeletal disorders is beneficial for workers, employers, and society. The results of this study will provide new information about the effectiveness of job rotation as a strategy to reduce work-related musculoskeletal disorders.

**Trial registration:**

NCT01979731, November 3, 2013

## Background

Ergonomic interventions to improve working conditions and to prevent the occurrence of occupational diseases have been widely used in industrial production lines [1]. In case of productive cells characterized by tasks that require some type of physical burden and/or the adoption of cognitive interventions to reduce the level or duration of exposure of workers, such as: redesign of jobs, suitable furniture and tools, ergonomic guidelines, rest breaks and rotation function [2]. The latter, considered organizational measures are generally adopted in tasks whose exposure level cannot be lowered due to the characteristics of the job or through physical measures [3].

Job rotation is one of the most practiced organizational interventions, such as cost reduction and/or prevention and health promotion for workers. Cost reduction is achieved by training workers to perform a greater number of functions for flexible allocation of worker activity. The prevention and health promotion for workers occurs through switching between different tasks with different levels of exposure and biomechanical applications, which in theory reduce the cumulative and or average exposure that should in turn promote the reduction of musculoskeletal and cognitive overloads [2,4].Thus, the job rotation has been adopted in repetitive, static, or monotonous activities, aiming to relieve the effects of muscle and cognitive overload, monotony, absenteeism, and stress [5,6].

Regarding the assessment of the effectiveness of the job rotation and the prevention of musculoskeletal complaints strategy, studies show conflicting results. Hinnen et al. evaluated supermarket workers by a cross-sectional study and found a 40% reduction in complaints of neck pain and a 20% reduction in complaints of pain in the shoulder for those who carried out labor [7]. Another study compared groups who performed or did not perform job rotation, and also found significant reductions in physical burden on workers of a garbage collection department who underwent rotation between the driving task and collecting trash [8]. However, while performing in a longitudinal study, it was observed that in the long run, the job rotation increased overload on other body regions, and workers began to report more back pain, especially in the group who had just completed the driving task [9]. Probably, it is because the groups continued exposure to the same risk factors, even when switching the task. Similar results were obtained by Frazer et al. [10], who evaluated two tasks of material handling, with low and high overhead level. The risk of lower back pain increased as a greater amount of time was used to perform the task with higher overhead, due to the cumulative and peak force [10].

The different study methods and criteria used for deployment of job rotation may partly explain the heterogeneity of results. This, plus the absence of clinical, controlled, randomized studies evaluating the effectiveness of the job rotation and the prevention of musculoskeletal complaints strategy, complicates the clinical decision making of professionals in the health and safety of the worker.

Importantly, positive results for the worker's health will only be achieved if the planning of the job rotation meets some important criteria such as number of workers and tasks involved, exposure level, requested body region, frequency of movements, duration of exposure, and duration of rest break, among others [11]. To assist in this planning, some methods and algorithms have been developed using the variables mentioned before [11-14]; however, the proposed rotation as reported in the literature, has not been evaluated in controlled clinical studies or randomized, and the effect of reducing absenteeism caused by musculoskeletal disorders in the workplace is not yet proven.

All these limitations point to the need for implementing a well design job rotation program along with a well-designed intervention study in order to fully and robustly evaluate the theory of job rotation and its application. Hence, we aimed to develop such a well-designed job rotation program that has specific criteria to reduce the cumulative and average biomechanical exposure and then to evaluate the effect of this newly developed job rotation program in the prevention of musculoskeletal disorders in industrial textile workers.

## Methods

### Study design, approval and registration

This is a randomized cluster controlled trial, prospectively registered, and with blinded assessment will be used to investigate the effectiveness of job rotation to prevent musculoskeletal disorders in industrial workers. The procedures and consent form were approved by the Research Ethics Committee of Cidade de São Paulo University (protocol no. 18170313.5.0000.0064) and were prospectively registered at ClinicalTrials.gov – NCT01979731. The study is being funded by the National Counsel of Technological and Scientific Development (CNPq), Brazil (473651/2013-0).

### Study population and setting

Study participants will be production line workers, recruited from the textile industry of a large company in Bahia, Brazil. The productive sectors of this industry will be classified according to the level of exposure to risk factors for musculoskeletal pain and disorders. The sectors to be included should have production lines that allow switching between tasks with different biomechanical demands and levels of risk for musculoskeletal pain and disorders, and further, that the work is carried out in cell production. Sectors whose production lines are automated or semi-automated, possessing the pace of work determined by machinery where work stoppage is not possible will be excluded. All workers in selected sectors will be invited to participate in the study.

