### Sample size calculation

The number of working hours lost due to sick leave by musculoskeletal injuries (M Group International Classification of Diseases, ICD-10) was used to estimate the sample size. The average time lost during the last three months in companies that the study observed was approximately 1,100 hours. The authors assume that interventions will enable a reduction of this number by 10%, that is, the groups will have a difference of 100 lost working hours, with a standard deviation of 250 hours. A statistical power of 80%, an alpha of 5%, and a possible sample loss of up to 15% is considered. Therefore, 116 participants are needed per group, or 232 in total. But, in this study the calculation of sample size was made by clusters and considered the number of production sectors included. The clusters number was four sectors (n = 957). The intervention group has 504 workers selected from Finishing Socks and Finishing Underwear departments, and the control group is 453selected from Sewing Socks and Sewing Underwear departments (Figure 1).

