### Assessment instruments and outcomes

Although the intervention is applied to the production sectors, the outcomes are on an individual level, since they reflect aspects of the health of workers. Data regarding outcome measures will be assessed at baseline and after 3, 6, and 12 months, except for information relating to removal for sick leave, which will be recorded daily. After a period of 12 months, the sector that had received only ergonomic guidelines will receive job rotation considering the hypothesis of this study in relation to its effectiveness. Both groups of workers will be monitored in a longitudinal study in subsequent months and compared to other workers identified within the criteria for risk analysis for 24 months.

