### Primary outcome measure

#### ***Absence from work due to sick leave***

In this study, we will use the sick leave for sick leave due to illness of the musculoskeletal system and connective tissue as a primary outcome measure. This outcome will be measured by the number of working hours lost due to the removal of a symptom or disease of the musculoskeletal system and connective tissue. These data will be obtained from records of medical certificates validated by the Human Resources department (HR) of each industry. Information regarding the clinical diagnosis and body region will also be collected using the specific codes of the International Classification of Diseases, 10th revision (ICD-10).

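### The aim is prevention, but the primary outcome is total certified musculoskeletal hours lost, and nothing separates leave already open when rotation starts from new episodes

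*Protocol article*

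**What the plan says.** The Background section of the protocol article gives the aim as "to evaluate the effect of this newly developed job rotation program in the prevention of musculoskeletal disorders in industrial textile workers". Study population and setting lists inclusion and exclusion rules for sectors and then says "All workers in selected sectors will be invited to participate in the study". No rule at worker level is stated. Sample size calculation counts 504 intervention and 453 control workers, 957 in four sectors.

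The primary outcome, under Absence from work due to sick leave, is the "number of working hours lost due to the removal of a symptom or disease of the musculoskeletal system and connective tissue". On the source it says: "These data will be obtained from records of medical certificates validated by the Human Resources department (HR) of each industry". ICD-10 codes are collected with these records. Under Assessment instruments and outcomes, outcomes are measured at set visits, "except for information relating to removal for sick leave, which will be recorded daily", and the control sectors receive rotation after 12 months. Statistical analysis names linear mixed models and intention to treat. It names no adjustment for leave at baseline.

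The planning figures are in Sample size calculation: "The average time lost during the last three months in companies that the study observed was approximately 1,100 hours", a 10% reduction, and "the groups will have a difference of 100 lost working hours, with a standard deviation of 250 hours".

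**The concern.** Hours lost are the number of episodes multiplied by their duration. Prevention concerns the first factor and, for new episodes, the second. An absence that began before rotation started cannot have been prevented by it, yet the outcome definition has no onset condition, so its remaining hours fall within the total.

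This matters because of the structure of the trial. Only two sectors are allocated to each arm. They were grouped by exposure level, and no balancing on existing leave is mentioned. A small number of long absences could fall mainly in one arm. A difference in total hours could then reflect who was already off work on day one, and a reader could not tell this from the planned result.

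**Working it through.** **The plan's own figure.** With a difference of 100 h, SD 250 h, two-sided alpha 5% and power 80%, the normal formula gives n per group = 2 × (1.960 + 0.842)² × (250/100)² = 98.1. Allowing for 15% loss, 98.1/0.85 = 115.4, rounded up to 116. The stated 116 per group (232 in total) reproduces, so this point exposes no arithmetic error.

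**What the 1,100 h can mean.** The article gives no unit. Assume a week of 40 to 44 h. One worker absent for a whole quarter loses 13 × 40 = 520 h to 13 × 44 = 572 h. That is the most one person can lose in three months, and 1,100 h is about twice as much. The figure therefore cannot be an average per worker. It must be a total over a group.

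**Scale over the controlled period.** Assume that the quarterly rate is constant and that the total refers to a group comparable with one arm.
- 12-month total: 4 × 1,100 = 4,400 h.
- Assumed effect: 10% of 4,400 = 440 h (or 4 × 100 = 400 h from the rounded difference).
- One open absence lasting the first quarter: 520/4,400 = 11.8% to 572/4,400 = 13.0% of the total.
- Against the effect: 520/440 = 1.2 to 572/440 = 1.3 times.

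**Sensitivity to the group that 1,100 h describes.** The article speaks of companies observed and does not define the group.

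| 1,100 h per quarter covers | 12-month total per arm | One open absence as share | Against a 10% effect |
|---|---|---|---|
| both arms together | 2,200 h | 23.6 to 26.0% | exceeds 220 h |
| one arm | 4,400 h | 11.8 to 13.0% | exceeds 440 h |
| one sector | 8,800 h | 5.9 to 6.5% | below 880 h; two absences (1,040 to 1,144 h) exceed it |

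On any of these readings, one or two long open absences in the same arm are as large as the effect sought.

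**What cannot be computed.** The documents do not say how many workers are on leave at the start, or what share of the 1,100 h came from open episodes.

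**The case against.** The strongest objection is that this rests on silence. The article does not say that open episodes are counted. The start of the counting window may be in a full protocol that is not shown, and workers on leave might be missed at invitation. That is fair as far as the counting rule goes. But the choice of total hours as the measure of prevention is stated, with unit, source and coding, and the definition has no onset condition.

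Second, total hours is a legitimate outcome. The Background and Discussion also frame the question as reducing absenteeism, and the 10% effect is set on total hours, so planned effect and outcome match. Rotation might also speed return to work or reduce relapse. All of this stands. It is a reason to keep total hours, but not a reason to read it alone as evidence on prevention.

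Third, the sample size formula treats 100 h and 250 h as values per participant. On that reading one absence moves an arm mean by only 520/504 = 1.0 h to 572/453 = 1.3 h, about 1% of 100 h. But this reading requires a mean of 1,100 h per worker per quarter, which no worker can reach.

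Fourth, an outcome restricted to new episodes has its own flaw. Workers still on leave cannot start a new episode, so they contribute structural zeros, and a sector with more open leave would look healthier. This stands. The new-episode analysis therefore needs a proper time at risk and should not simply replace total hours.

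**Conclusion.** The point holds as a mismatch between aim and outcome that the plan leaves unresolved. Leave open at the start and new leave are pooled in the primary outcome, and with two sectors per arm a single quarter-long open absence (520 to 572 h) can exceed the assumed 10% effect (about 440 h of 4,400 h over 12 months). This size rests on three assumptions: a 40 to 44 h week, a constant quarterly rate, and a 1,100 h total that refers to a group comparable with one arm.

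A reader might infer more, and the documents do not support it:
- That the result will be biased. The number and distribution of open episodes are not given.
- That one absence is about half of all hours (520/1,100 = 47% to 572/1,100 = 52%) and over five times the target. This sets it against three months of leave, although the controlled comparison runs for 12.
- That workers on leave at the start never rotate. They may return during the 12 months.
- That every worker is enrolled and every lost hour counted. Workers are invited, and only certified musculoskeletal leave counts.
- That power is lost. The planned effect is already on the scale of total hours.

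**What to change.** Use the HR certificates that already supply the primary outcome.

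1. Set one common start date for counting in all four sectors.
2. Pre-specify, beside total hours, an analysis of new musculoskeletal episodes per worker and of the hours from episodes first certified on or after that date.
3. For workers on leave at the start, count time at risk for a new episode only from return to work.
4. State how renewals of earlier certificates are linked to the episode they continue. This needs the first-certificate date of any leave open at the start; the article does not say whether it is collected.
5. Either adjust the total-hours analysis for leave open at the start, or show it with and without those hours.
6. For the Nordic items, report new symptoms among workers symptom-free at baseline beside overall prevalence. Use the same item to define both, because the 12-month recall at the 3- and 6-month visits reaches back before baseline.

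No worker is dropped from the intention-to-treat comparison of total hours. The cost is a little more analysis work, a look-up of certificate dates, and slightly fewer hours in the new-episode count.

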### Sample size calculation

The number of working hours lost due to sick leave by musculoskeletal injuries (M Group International Classification of Diseases, ICD-10) was used to estimate the sample size. The average time lost during the last three months in companies that the study observed was approximately 1,100 hours. The authors assume that interventions will enable a reduction of this number by 10%, that is, the groups will have a difference of 100 lost working hours, with a standard deviation of 250 hours. A statistical power of 80%, an alpha of 5%, and a possible sample loss of up to 15% is considered. Therefore, 116 participants are needed per group, or 232 in total. But, in this study the calculation of sample size was made by clusters and considered the number of production sectors included. The clusters number was four sectors (n = 957). The intervention group has 504 workers selected from Finishing Socks and Finishing Underwear departments, and the control group is 453selected from Sewing Socks and Sewing Underwear departments (Figure 1).

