## Discussion

This study design was developed to investigate the effectiveness of job rotation to prevent musculoskeletal disorders in industrial workers. Despite being a topic of great relevance, due to the difficulty of completely reducing the risk factors of the work environment, few studies have evaluated the effect of job rotation in reducing absenteeism caused by musculoskeletal disorders. It is expected that interventions to reduce the occurrence of musculoskeletal disorders and the consequent removal of the workers for sick leave, 100 hours of lost work. It is also hoped that the results obtained in this study may contribute to setting standards in the field of Occupational Health, as well as for decision making of professionals working in this area.

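### The 1,100 h, 100 h and 250 h behind 116 per group carry no unit and cannot be per-worker values, so the stated 80% power is not valid for the individual-level primary outcome

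*Protocol article*

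**What the plan says.** The protocol article's Sample size calculation starts from sick leave for musculoskeletal conditions: "The average time lost during the last three months in companies that the study observed was approximately 1,100 hours". It assumes a reduction of 10% and concludes that "the groups will have a difference of 100 lost working hours, with a standard deviation of 250 hours". The error rates and attrition follow: "A statistical power of 80%, an alpha of 5%, and a possible sample loss of up to 15% is considered". The result is 116 participants per group, 232 in total.

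The same paragraph then says that the size was in fact worked out by clusters, and reports four sectors with 957 workers (504 intervention, 453 control). It gives no other effect size, SD or power for that design.

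On the level of the outcome, Assessment instruments and outcomes says: "Although the intervention is applied to the production sectors, the outcomes are on an individual level". The Discussion repeats the expected benefit as a reduction in "the consequent removal of the workers for sick leave, 100 hours of lost work", again without unit or period.

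**The concern.** A two-group comparison of means returns a number of workers only if the difference and the SD are hours per worker. The starting figure is attributed to companies, has no denominator, and is too large to be one worker's lost time in a quarter. An aggregate therefore seems to have been entered as though it were a between-worker mean.

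This paragraph is the only quantitative justification for the primary outcome. If its inputs are in the wrong unit, the trial has no valid statement of the power it has, and the 100 h in the Discussion would mislead anyone who set the trial's per-worker estimate against it.

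**Working it through.** **1. Reproduce the plan's figure.** Inputs from Sample size calculation: difference 100 h, SD 250 h, alpha 5% (two-sided assumed, since sidedness is not stated), power 80%, loss 15%.

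- n per group = 2 × (1.960 + 0.842)² × (250/100)² = 2 × 7.849 × 6.25 = 98.1
- After loss: 98.1 / 0.85 = 115.4, rounded up to 116, as stated.
- A one-sided test gives 78 per group, or 92 after loss, which does not match.

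So 100 h and 250 h were used as a between-worker difference and SD, with a standardised difference of 100/250 = 0.40.

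**2. Can 1,100 h be a per-worker mean?** Three months is about 13 weeks, and 1,100/13 = 84.6 h lost per week. The documents give no scheduled hours, so a range is assumed:

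| Assumed week | Scheduled hours in 13 weeks |
|---|---|
| 36 h | 468 |
| 40 h | 520 |
| 44 h | 572 |
| 48 h | 624 |
| 60 h | 780 |

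Complete absence of every worker would still fall short of 1,100 h. Averaging only over workers on leave does not help, because the ceiling applies to each worker.

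**3. What an aggregate implies per worker.** The denominator is not stated, so both rows are assumptions.

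| 1,100 h is | Workers | Mean per worker | 10% of mean |
|---|---|---|---|
| a total over all trial workers | 957 | 1,100/957 = 1.15 h | 0.115 h |
| an average total per sector | 957/4 ≈ 239 | 1,100/239 = 4.6 h | 0.46 h |

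If the average were instead a monthly total, these means would triple to about 3.4 and 13.8 h, and the 10% reductions to about 0.3 and 1.4 h. A workforce larger than 957 would lower them.

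**4. Does the SD of 250 h fit?** For values between 0 and M with mean m, the SD cannot exceed √(m(M − m)). With M = 572 h, the ceiling is √(1.15 × 570.85) = 25.6 h for the first row and √(4.6 × 567.4) = 51 h for the second. With M = 780 h, the ceilings are 29.9 h and 59.7 h. An SD of 250 h is impossible in every case.

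**5. Could 0.40 survive a change of unit?** If 1,100 and 250 simply scaled down together, the coefficient of variation would be 250/1,100 = 0.227. When a fraction p of workers has any leave and the rest have zero, the coefficient of variation is at least √(1/p − 1). A value of 0.227 therefore requires p ≥ 1/(1 + 0.227²) = 0.95, so about 95% of workers would need musculoskeletal sick leave in the period. With p = 50% (assumption), a 10% reduction is at most 0.10 SD. That needs 2 × 7.849/0.10² ≈ 1,570 per arm, and 504 versus 453 workers give at most about 34% power, before any clustering.

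**6. Could 100 h and 250 h be sector totals?** Then n counts sectors, not participants. With two sectors per arm, a t test on 2 degrees of freedom has about 6% power.

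**The case against.** The strongest reply is that this calculation does not set the size of the trial. The protocol puts 116/232 aside in the next sentence and fixes enrolment by four sectors, and Study population and setting invites every worker in them. This stands. A reader might infer that the trial enrolled the wrong number because of the 100 h, but the documents do not support that. Correcting the paragraph changes neither enrolment nor allocation. What fails is the power statement, and no other is offered.

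Second, a reader might infer that the trial has no usable target difference. That also goes too far: the 10% relative reduction is free of units and can be applied once a per-worker baseline is known. Only its conversion to 100 h with SD 250 h fails.

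Third, the factor by which 100 h is too large depends on a denominator that the protocol does not give. Dividing by all 957 workers makes 100 h about 870 times the 10% reduction (100/0.115), but dividing by sector makes it about 217 times (100/0.46). No single multiple should be quoted. That the 1,100 h is an aggregate is itself an inference, though the likeliest one; a misreported figure or period cannot be excluded.

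Two further criticisms carry little weight. Ten per cent of 1,100 is 110, not 100, but the baseline is approximate and the smaller difference is conservative (116 against 96 per group). Planning from a three-month baseline is not in itself an error, and neither place says that the 100 h is a 12-month difference. The exact outcome window may also be set in a fuller document that is not shown.

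**Conclusion.** The point holds as a unit error in the inputs; the formula itself was applied correctly. The three figures in hours have no stated unit, yield 116 only when read as per worker, and cannot be per worker at any assumed working week from 36 to 60 h. Under the two quarterly aggregate readings, a 10% reduction is about 0.1 to 0.5 h per worker instead of 100 h. The standardised difference of 0.4, the 116/232 and the 80% power are therefore not valid for the individual-level primary outcome, and the 100 h in the Discussion inherits the problem.

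No corrected sample size can be derived, because the protocol gives neither a per-worker mean nor a per-worker SD. The impossibility rests on the assumed working week; the size of the restated effect rests on the assumed denominators. The conclusion concerns what the trial can claim about its power, not the number of workers enrolled.

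**What to change.** - State the unit, denominator and period of the 1,100 h.
- From the Human Resources records that supply the primary outcome, take the mean and SD of musculoskeletal hours lost per worker, counting workers with none as zero, over the period of the primary comparison.
- Restate the target as 10% of that mean.
- Replace the 116/232 and the 80% power with the power or precision that four sectors and 957 workers give, allowing for clustering.
- Remove the 100 h from Sample size calculation and the Discussion, or label it correctly once its unit has been confirmed. It should not be called a company total on inference alone.

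The cost is one per-worker data extract, if the baseline records are held in that form (the protocol does not say), and a rewritten paragraph. No extra enrolment is needed. The downside is that the stated power will be less favourable.

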### Randomization

Randomization was performed at the group level (departments/productive sectors), in order to avoid contamination from workers allocated in the intervention to those in the control group. The productive sectors included in the study were pre-stratified by the level of exposure to risk factors for musculoskeletal pain and disorders. Sectors with similar demands were grouped and randomly divided between intervention and control groups. Using a computer-generated randomization (http://www.randomizer.org) with random numbers to define groups, the randomization was performed by an independent researcher who was not involved in recruitment and assessment. Sealed envelopes will be used. The randomization was performed before baseline measurements.

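### The 80% power and 116 per group come from a formula for independent workers; with two sectors per arm the trial has that power only if the ICC is essentially zero

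*Protocol article*

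**What the plan says.** The Sample size calculation section of the protocol article takes working hours lost to musculoskeletal sick leave as the basis. It assumes that "the groups will have a difference of 100 lost working hours, with a standard deviation of 250 hours", with 80% power, 5% alpha and up to 15% loss. It then states: "Therefore, 116 participants are needed per group, or 232 in total. But, in this study the calculation of sample size was made by clusters". What follows that second sentence is a count of sectors and a headcount: "The clusters number was four sectors (n = 957").

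The rotation arm consists of two finishing departments: "The intervention group has 504 workers selected from Finishing Socks and Finishing Underwear departments". For the comparison arm, which consists of two sewing departments, the section says: "the control group is 453selected from Sewing Socks and Sewing Underwear departments". The Abstract repeats the total: "A total cluster will be 4 sectors, and 957 workers will be recruited from a textile industry and randomly allocated". The Randomization section confirms the unit: "Randomization was performed at the group level (departments/productive sectors"). The section on assessment instruments and outcomes adds: "Although the intervention is applied to the production sectors, the outcomes are on an individual level".

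**The concern.** Sectors are randomised and workers are measured, so workers in the same sector share whatever is particular to that sector. A sample size for such a trial has to include an ICC and the number of sectors. The section says the calculation was done on a cluster basis, yet every input it lists belongs to a calculation for independent individuals. According to the section on study population and setting, all workers in the selected sectors are invited, so 957 is the number available and not a computed requirement.

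What is at stake is how the result will be read. A reader who sees 232 required and 957 enrolled will assume ample power, and could take a non-significant result as evidence that job rotation has no effect when the trial had little chance of showing one. The Discussion hopes the findings will help to set occupational health standards, so that misreading would matter.

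**Working it through.** **Inputs from the Sample size calculation section:** difference 100 h; SD 250 h; power 80%; alpha 5% (taken as two-sided, which reproduces the stated figure); loss 15%; 504 and 453 workers; two sectors per arm; mean sector size 957/4 = 239.25. **Assumed:** the ICC, because the document gives none, and equal sector sizes within each arm (252 and 226.5).

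**Step 1: reproduce the plan's figure.** For independent workers,

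n per group = 2(1.960 + 0.842)²(250/100)² = 98.1, and 98.1/0.85 = 115.4, rounded up to 116.

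The stated 116 is fully accounted for, with no room for a design effect.

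**Step 2: variance for the design used.** With two equal sectors in each arm,

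Var(difference) = 250² × [ICC + (1 − ICC)(1/504 + 1/453)].

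The between-sector term (the first ICC in the bracket) does not shrink as workers are added. Only more sectors reduce it.

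**Step 3: power.** Four sectors less two arms leaves 2 df, with critical t 4.303. Power comes from the noncentral t with noncentrality 100/SE. The difference detectable with 80% power is 5.65 × SE. The design effect is 1 + 238.25 × ICC. The column headed Normal applies the design effect but treats the between-sector variance as known.

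| ICC (assumed) | Design effect | Equivalent independent workers | SE (h) | Power, 2 df | Power, Normal | Detectable difference, 2 df (h) |
|---|---|---|---|---|---|---|
| 0 | 1.0 | 957 | 16.2 | 85% | >99% | 91 |
| 0.001 | 1.2 | 773 | 18.0 | 79% | >99% | 102 |
| 0.005 | 2.2 | 437 | 23.9 | 59% | 99% | 135 |
| 0.01 | 3.4 | 283 | 29.7 | 45% | 92% | 168 |
| 0.02 | 5.8 | 166 | 38.8 | 31% | 73% | 219 |
| 0.05 | 12.9 | 74 | 58.1 | 18% | 41% | 328 |

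Example at ICC 0.01: the bracket is 0.01 + 0.99 × 0.00419 = 0.01415; SE = 250 × √0.01415 = 29.7 h; noncentrality = 100/29.7 = 3.36; power 45%; detectable difference 5.65 × 29.7 = 168 h.

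**Step 4: where 80% is reached.**
- All 957 workers on 2 df: ICC of 0.0008 or less.
- After 15% loss: power is about 80% at ICC 0, and the limit falls to about 0.0001.
- Unlimited workers per sector: ICC of about 0.005 or less.
- The stated 232 workers in four sectors: power is 40% at ICC 0, 29% at 0.01 and 16% at 0.05.
- At 239 workers per sector, 80% power would take 3, 4 and 7 sectors per arm at ICC 0.01, 0.02 and 0.05.

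**Step 5: a check without a model.** Four sectors can be divided two against two in 6 ways, so a re-randomisation test cannot give a two-sided p-value below 2/6 = 0.33. If the draw was made within two pairs there are 4 allocations and the floor is 2/4 = 0.50. No such test is planned. The figures only show how little information four randomised units carry.

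**The case against.** The best counter-argument is that the text moves on from 232 and takes 957, which is 957/232 = 4.1 times as many. With the design effect alone and a Normal reference, 957 workers keep 80% power up to an ICC of about 0.016. The Statistical analysis section plans linear mixed models and does not fix the degrees of freedom. It is true that the severity of the result comes more from having four sectors than from the number of workers. The Normal column, however, treats the between-sector variance as known when it must be estimated from four sectors, and fitting a mixed model does not remove that limit.

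The 2 df are also open to question, because the Randomization section describes stratification by exposure and a division of similar sectors. If the analysis keeps two matched pairs, 1 df remains and power is about 37% even at ICC 0, before any gain in precision from matching. The 2-df analysis is therefore the more favourable of the two on degrees of freedom.

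Three smaller points stand. The article does not say outright that 116 per group suffices for the cluster trial; the fault is a claimed cluster calculation whose inputs contain none. As a condensed article it may omit a fuller calculation, but it lists every other input. Finally, the hour figures are only as sound as the plan's 100 h and 250 h. The baseline of 1,100 h over three months exceeds what one worker could work (13 weeks at an assumed 40 to 48 h gives 520 to 624 h), so it looks like an aggregate. The power figures depend only on the ratio 100/250 = 0.40 and the ICC, but the detectable differences in hours should be read with that caution.

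**Conclusion.** The concern holds. The arithmetic behind 116 is correct for independent workers and does not apply to this trial. At the plan's own standardised difference of 0.40, two sectors per arm on 2 df give 45% power at ICC 0.01 and 18% at ICC 0.05, and 80% is reached only at an ICC of about 0.0008 or less. An ICC that small is hard to defend when the sectors are different departments that were stratified because their exposure differs. The result rests on an assumed range of ICCs, equal sector sizes within arms, and an unpaired cluster-level test. The claim of 80% power needs correcting before the trial's result is interpreted.

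**What to change.** Rewrite the second half of the sample size paragraph:

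- Remove the claim of 80% power for this design, any implication that 116 per group is sufficient, and the statement that the calculation was done by clusters.
- State the design as it is: four sectors, two per arm, mean size 239, with 957 being all workers available in those sectors.
- Tabulate power and detectable difference for ICC 0 to 0.05 on 2 df, and say that the ICC values are assumed. If the analysis keeps the sectors as matched pairs, give the table on 1 df. Confirm whether the 100 h and 250 h are per-worker values before quoting differences in hours.
- Declare the primary result to be the estimated difference with a confidence interval on the same degrees of freedom, and say that absence of significance will not be read as absence of effect.

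The cost is one reworded paragraph and a less favourable statement of power. No workers are added.
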